### Sample size

Approximately 60 participants will be enrolled in each treatment arm through pro-active case-finding methods. Approximately 60 participants were enrolled for each arm in a previous Group PM+ feasibility trial [5]. Because power calculations will not be carried out for this trial, 60 participants, or 7–10 groups, per arm will provide enough relevant information to inform feasibility and acceptability for the definitive effectiveness RCT following the trial. In addition, approximately 15 trial participants will be recruited for the qualitative interviews, as well as 15–18 additional key informants from the community. We also anticipate conducting qualitative interviews with research and psychosocial staff.

### Financial incentives

Participants will receive compensation in the form of household goods (e.g., soap, toothpaste) equivalent to 100–200 Nepali Rupees per assessment, to compensate for time invested in the research. Assessments will take a maximum of 1 h and 30 min, and participants will be informed of this time frame as part of the consent process. Participants will not be compensated monetarily for the time they spend in the sessions. For those in the treatment arm, snacks and tea will be offered to the participants at every session. Travel costs to sessions and to assessments will be compensated for as well. Actual cost basis is not currently feasible because of the unavailability of local transport receipts but a fixed amount for compensation will be calculated based on the area that they come from.

### Data management and monitoring

All principal investigators (PI) on the study will have access to primary data. The site PI will conduct quality assurance checks on data collected by the research assistants who will use a password-protected tablet to collect data. The data on the tablet will be synchronized and uploaded in the Open Data Kit (ODK) daily, saved on a private server, and transferred to a data-analytic computer program (e.g., SPSS) without the identifying key. Results will be published regardless of being negative or positive results and submitted to peer-reviewed scientific journals. A Data Safety Monitoring Committee (DSMC) will be established specifically for oversight of the trial and review of serious adverse events and adverse events. The DSMC will include psychiatrists, non-governmental organization experts in psychosocial programs, and researchers, and will determine any appropriate action in respect to ongoing trial conduct (e.g., referral to specialized care). The DSMC has the right to unblind at the individual level at any time.

### Planned analyses

#### Qualitative analyses

Focus group discussions (FGDs), key informant interviews, and process evaluation notes will be coded in NVIVO [35] and analyzed using content analysis [36] for themes of cultural acceptability, experience of CPSWs delivering Group PM+, adequacy of training duration, structure of training, content of training, and follow-up engagement, following approaches used in similar global mental health studies [37]. Coding will be done by multiple independent raters, and inter-rater reliability will be calculated using Kappa scores. Data analysis will be conducted throughout each step to facilitate iterative revision then finalization of the manual. Following the Consolidated Criteria for Reporting Qualitative Studies (COREQ), we will document the process according to the 32-item checklist [38]. Broadly, for domain 1 “research team and reflexivity,” the qualitative research team will include the PIs and TPO staff; the degrees will range from MD, PhD, to MA and Bachelors; the occupations will include academic medical faculty, NGO staff, and members of WHO; there will be both male and female qualitative staff; staff experience in qualitative research will range from 1 month to greater than 10 years; the relationship with participants will not precede the study; participants will know that research staff are employed by or associated with TPO Nepal; and interviewer characteristics (age, education, region of origin, etc.) will be reported. For study design, content analysis will be used; selection will be reported as described above; setting features including location and presence of non-participants will be reported; an interview guide will be used; there will be repeat interviews at different times in the training and supervision timelines; audio will be recorded; duration will be documented; data saturation or lack thereof will be reported; and transcripts will not be returned to participants for analysis. There will be approximately four coders; the coding tree will be published; themes will be identified in advance with the option to generate additional themes; participants will not provide feedback on the coding; quotations will be presented; data and findings will be consistent; and major and minor themes will be clearly presented.

#### Statistical analyses

We will employ statistical analyses comparable to those used in another pilot c-RCT being conducted in Nepal [39]. The quantitative outcomes of interest (Table 4) will be summarized descriptively using appropriate summary statistics (mean and standard deviation for continuous outcomes and numbers and proportions for categorical outcomes) and graphically over time for both study arms. Trends for each score will be plotted to examine between- and within-person differences and to determine the plausible pattern (e.g., linearity) of those trends. As noted by Eldridge et al., there are concerns that sample size estimates based on this trial’s data could be too small; therefore, we will also draw upon other studies in Nepal to inform the subsequent effectiveness study sample size [40]. We plan to power the full trial based on conservative estimates of the parameters of interest rather than exclusively those obtained from this c-RCT by using the upper bound of the 95% CI for the intra-class correlation coefficient (ICC) and by comparing our estimates to those from other studies of similar outcomes to be sure we will increase our estimates if we find them to be considerably smaller than those from other studies. By using such a “triangulation” approach and by obtaining context-specific data, we are confident that we will be able to better design the full-scale c-RCT than in the absence of the feasibility c-RCT data. The data will also be used to inform the choice of effect estimate (e.g., difference in slopes or in means at a specific follow-up time point) in the future c-RCT that will build on the current study. Preliminary indicative estimates of differences in primary and secondary outcomes by arm will be obtained. In practice, we will power the future c-RCT predominantly based on magnitudes of effect that are of public health relevance rather than using magnitudes of effects obtained from the study, which will not necessarily be indicative of what could be attained in an appropriately powered larger c-RCT.

**Table 4 Tab4:** Quantitative outcome measures

Construct	Instrument	Description	Assessment time periods		
			Enrollment (−*t*_1_)	Baseline (*t*_0_)	Follow-up (*t*_1_)
Primary outcome (participants)					
Depression symptoms	Patient Health Questionnaire (PHQ-9)	Participants rate depression symptoms over past 2 weeks		X	X
Secondary outcomes (participants)					
Daily functioning	WHODAS	Participants rate their ability to engage in daily activities	X		X
General psychological distress	General Health Questionnaire(GHQ-12)	Participants measure their general psychological distress	X		X
General psychological distress	Somatic symptoms of Nepali Psychosocial and Mental Health Problems (PMHP)	Participants rate their somatic symptoms related to psychosocial health		X	X
General psychological distress	Heart-mind	Participants note if they have had any “*man ko samasya*” or heart-mind problems recently	X	X	X
General psychological distress	Tension Checklist	Participants note if they have had any tension recently		X	X
Alcohol use disorder	Alcohol Use Disorders Identification Test (AUDIT)	Participants rate alcohol use and associated behavior, as well as daily ethanol consumption	X		
Post-traumatic stress symptoms	PTSD Checklist for DSM5 (PCL-5)	Participants rate their post-traumatic stress symptoms on a scale		X	X
Personalized outcome	Psychological Outcome Profiles (PSYCLOPS)	Participants list their emotional and practical problems and rate how much each problem affects them		X	X
Additional measures of mechanisms and potential mediators					
Ways of coping	Reducing Tension Checklist (RTC)	Participants assess their own behavioral and psychosocial skills related to coping		X	X
Traumatic events	Traumatic Events Inventory (TEI)	Participants rate if they have been exposed to certain traumatic events throughout their lifetime		X	X
Perceived social support	Multidimensional Scale of Perceived Social Support (MSPSS)	Participants assess their own connectedness with close family, friends, and other forms of support		X	X
Suicidality	Suicidality	Participants rate if they have recently had suicidal thoughts, ideation, and plans	X		

#### Mixed methods framework

This feasibility study will follow the Good Reporting of A Mixed Methods Study (GRAMMS) guidelines: First, mixed methods are being used to evaluate feasibility and acceptability qualitatively while quantitative information will be used for the design of the full trial. Second, qualitative and quantitative will be assessed generally during the same intervals of the study after delivery of Group PM+. Both methods will be clearly documented in publications with regard to sampling, data collection, and analysis. Integration will occur in regard to qualitative descriptions of and quantitative scores on key variables. Because this is a feasibility study, inference testing on the quantitative data are limited; therefore, we cannot compare qualitative and quantitative data with regard to effectiveness of the Group PM+. Sixth, insights resulting specifically from integration of qualitative and quantitative will be highlighted.

### Ethics and research governance

#### Consent

The informed consent process will consist of two steps: informed consent for screening and informed consent for taking part in the Group PM+ trial. A research assistant will conduct informed consent for screening. When a possible participant screens positive, the CPSW will conduct a family session in which potential participants will decide if they would like to take part in Group PM+. The research assistant will ask the potential participant what family member they would like present for the consent procedure. Potential participants also have the option of not including a family member in the consent process. With this model, the participant can gain support from their family in deciding if they would like to participate in the trial. In either phase of the consent process, it will be made clear that refusal to participate will not have an impact on any type of support they receive and that they will still be referred to local mhGAP-trained health workers and a counselor if needed.

#### Harms

The main risk is potential psychological distress among participants of the intervention arm depending on the type of interactions with other group members and group facilitator. Participants can stop their involvement in the trial at any point. All patients referred to mhGAP-trained health workers and TPO counselors are expected to be receiving quality clinical care and management of adverse events. Primary healthcare workers are supervised by a psychiatrist in Kathmandu who can provide information on medications and receive referrals for patients with worsening symptoms or other clinical concerns.

All changes in treatment resulting from adverse events or serious adverse events will be reported to the DSMC in Nepal. TPO Nepal is responsible for the data collection and storage and making data available to the DSMC, funders, and IRBs for audits when appropriate.

#### Post-trial care

Group PM+ facilitator training will be provided to those that attended CPSW basic training in the control arm after the trial. Though they will not be compensated through TPO, facilitators in the control arm could deliver Group PM+ sessions post-trial to their community with support from the local government. Primary healthcare workers will remain in the VDC and continue to provide mental health care for members of the community and Group PM+ trial participants.

### Dissemination

Findings from the feasibility study will be published in academic journals, disseminated through the Mental Health Innovation Network (www.mhinnovation.net), and reported to research funder (Office of U.S. Disaster Foreign Assistance/USAID). Findings will also be disseminated in Nepali and English to key stakeholders including district, provincial, and national government through reports and presentations. Authorship eligibility will comply with guidelines of the International Committee of Medical Journal Editors, with additional attention to recommendations for equitable representation of researchers from LMIC for academic authorship [41]. In keeping with transparency recommendations, data will be made publicly available after publication of primary analyses.

### Timescale

Participants for the Group PM+ trial will be recruited starting approximately 3 months after the initial CPSW training (see Table 5 for SPIRIT enrollment and assessment schedule). Group PM+ sessions will begin for those in the intervention arm within a maximum of 2 weeks after consent. Within these 2 weeks, baseline will be conducted for both arms. End line will be collected a week to a week and a half after the intervention is complete in the intervention arm and eight to eight and a half weeks after initial screening in the control arm. We anticipate that the trial will conclude by spring 2018.

**Table 5 Tab5:** Schedule of enrollment, interventions, and assessments for Group PM+

	Study period		
PARTICIPANTS (*direct beneficiaries*)—participants of Group PM+ or control arm			
	Enrollment	Baseline	Follow-up
Timepoint	*− t* _1_	*t* _0_	*t* _1_
Enrollment			
Allocation	X		
Eligibility screen	X		
Informed consent	X	X	
Interventions			
PM+	X	X	X
Control	X	X	X
Assessments			
GHQ-12	X		X
WHODAS	X		X
AUDIT	X		
Suicidality	X		
PMPH		X	X
PHQ-9		X	X
PCL-5		X	X
PSYCLOPS		X	X
RTC		X	X
TEI		X	X
Heart-mind	X	X	X
MSPSS		X	X
Tension Checklist		X	X

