RAs and research staff	Intervention and control (*n* = 8): RAs and Research Supervisor	KIIs, FGDs	After completion of intervention
Psychosocial staff	Intervention and control (*n* = 3): Clinical Supervisors and counselor	KIIs, FGDs	After completion of intervention

Though the clinical outcomes in this feasibility and acceptability trial are secondary, the ability to measure them and have fewer than 15% missing items is a feasibility outcome. Clinical outcomes among participants will be measured through baseline (*t*_0_) and follow-up (*t*_1_) assessment. The baseline (*t*_0_) assessment will be conducted after the family meeting. The follow-up assessment (*t*_1_) will be scheduled 1–1.5 weeks after the fifth Group PM+ session (i.e., 8–8.5 weeks after the pre-intervention assessment). All instruments will be administered by trained research staff blind to the allocation status of the participants. The main analysis metric will be differences in primary and secondary outcomes between *t*_0_ and *t*_1_.

The primary clinical outcome measure will be the Patient Health Questionnaire (PHQ-9), a well-known 10-item instrument measuring symptoms of depression [19] (see Table 3). The measure has been clinically validated in Nepal [20]. There are eight secondary clinical outcome measures. To diminish the burden of time and questionnaires administered to the participants, many short-form versions of the assessments will be used. The WHO Disability Assessment Scale (WHODAS) has been used previously in Nepal [21–23], with excellent internal consistency between items (*α* = 0.90) and validity with multiple mental health measures for depression (*r* = 0.70, *p* < 0.001), anxiety (*r* = 0.64, *p* < 0.001), and PTSD (*r* = 0.37, *p* < 0.001). The GHQ-12 measures general psychological distress and has been clinically validated in Nepal [24]. The Psychosocial Mental Health Problems (PMHP) scale is a locally developed five-item assessment of common psychosocial problems [10]. The heart-mind screener is also locally developed and will be used to determine the acceptability of local idioms of distress and impairment due to these problems [20]. The PCL-5 (eight items) was shown in a recent study to have comparable diagnostic utility to the 20-item PCL-5 [25].

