### Recruitment

In the study VDCs, CPSWs will conduct awareness-raising activities to educate the public about availability of treatment for CMDs. In addition, female community health volunteers (FCHVs) and members of local community organizations (such as mothers’ groups, youth groups, etc.) will be trained on the Community Informant Detection Tool (CIDT) to identify people in the community with potential common mental disorders. The CIDT is a vignette-based tool for pro-active case detection by lay people, which has been developed and tested in Nepal [34]. The CIDT has a positive predictive value of 0.68 for adults [33]. The adapted version of CIDT for this study will include both inclusion vignettes (e.g., general distress, developed for the trial) and exclusion vignettes (e.g., psychosis, which have already been developed and validated). When community members and FCHVs identify a person in the community with symptoms of common mental disorders as described in the vignettes, they will ask them if they would like support for their stress-related problems. If people indicate they would like to receive support, then they will be told that a research assistant (RA) will visit them to conduct further screening. Individuals who meet CIDT criteria for exclusion conditions will be referred to local mhGAP-trained health workers. RAs will conduct additional recruitment by screening patients attending primary health care centers.

After screening by the RAs, CPSWs will hold a family meeting with the potential participant and a family member if they choose to have a family member participate. The family meeting will consist of (a) information about the results of the screening, (b) brief psychoeducation about the psychological consequences of adversity, and (c) information on seeking services from local health facilities with health care providers trained in basic mental health and psychosocial support. Those in the Group PM+ arm will also receive information about the intervention. Based on the family meeting, individuals can choose whether or not they want to enroll in their respective treatment arms and continue in the study.

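### The protocol counts the same 8–8.5 weeks to follow-up from two different starting points, baseline in one section and screening (controls only) in another, so equal follow-up in the two arms is not assured.

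*Protocol article*

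**What the plan says.** All references are to the protocol article.

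- **Measures/outcomes** schedules t1 at "1–1.5 weeks after the fifth Group PM+ session (i.e., 8–8.5 weeks after the pre-intervention assessment". It gives no separate rule for controls.
- **Timescale** keeps the window after treatment for one arm ("End line will be collected a week to a week and a half after the intervention is complete in the intervention arm") but sets t1 for the other at "eight to eight and a half weeks after initial screening in the control arm".
- **Order of steps.** Recruitment states "After screening by the RAs, CPSWs will hold a family meeting with the potential participant". Measures/outcomes says that the t0 "assessment will be conducted after the family meeting". Tables 4 and 5 list enrollment (−t1) and baseline (t0) as separate time points.
- **Windows.** Timescale says "Group PM+ sessions will begin for those in the intervention arm within a maximum of 2 weeks after consent", and then "Within these 2 weeks, baseline will be conducted for both arms".
- **Use of the interval.** Measures/outcomes makes the change from t0 to t1 the main analysis metric.
- **Exceptions at baseline.** Tables 4 and 5 take the first GHQ-12 and WHODAS values at enrollment, not at t0.

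**The concern.** The figure of 8–8.5 weeks appears in both sections but is attached to different events. A team following Timescale would book control follow-ups from the screening date. A team following Measures/outcomes would book them from the baseline date. Under the Timescale rule, equal follow-up in the two arms is not guaranteed.

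Participants are selected for high distress and impairment, so some improvement over time without treatment is plausible. If the arms are observed for different lengths of time, that improvement mixes with the arm difference in the t0–t1 change. Statistical analyses also says that the data will inform whether the full trial compares slopes or means at a fixed time, a choice that depends on when t1 falls. None of the five quantitative progression criteria looks at assessment timing. Procedures in domains that meet their criteria are to be retained, so the mismatch could pass into the full trial unnoticed.

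**Working it through.** **1. Is the pre-intervention assessment the same event as screening?** The text points to t0. Measures/outcomes says PSYCHLOPS is given pre-intervention and is skipped at session one because the two are close in time. Tables 4 and 5 schedule PSYCHLOPS at t0 and not at enrollment.

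**2. How large can the gap be?** Let g be the time from screening to t0. The Consent section describes two consents. If Timescale means the screening consent, g is 0–2 weeks. If it means the trial consent, g is 0–2 weeks plus an unstated lag. Either reading allows g > 0, and neither gives its value.

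**3. Intervals if the Measures/outcomes figure holds for PM+.**

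PM+ t0–t1 = 8 to 8.5. Control t0–t1 = (8 to 8.5) − g. For GHQ-12 and WHODAS, control screening–t1 = 8 to 8.5 and PM+ screening–t1 = (8 to 8.5) + g.

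| g (weeks, assumed) | Control t0–t1 | PM+ t0–t1 | Control screening–t1 | PM+ screening–t1 |
|---|---|---|---|---|
| 0 | 8–8.5 | 8–8.5 | 8–8.5 | 8–8.5 |
| 0.5 | 7.5–8 | 8–8.5 | 8–8.5 | 8.5–9 |
| 1 | 7–7.5 | 8–8.5 | 8–8.5 | 9–9.5 |
| 2 | 6–6.5 | 8–8.5 | 8–8.5 | 10–10.5 |

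At g = 0.5 the two t0–t1 windows touch only at 8 weeks; above that they do not overlap. At g = 2 the control interval is shorter by 2/8.5 to 2/8, or 23.5% to 25%.

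**4. Does the 8–8.5 weeks reproduce from the session calendar?** PM+ t0–t1 = wait from t0 to session one (w) + length of the session block + 1 to 1.5. Spacing of the five sessions is not stated, so both lines below assume weekly sessions.

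- Five session-weeks: w = 2 gives 2 + 5 + (1 to 1.5) = 8–8.5; w = 0 gives 6–6.5.
- Four weeks from first to fifth session: w = 2 gives 7–7.5; w = 0 gives 5–5.5.

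The stated figure results from one set of assumptions and not from others. It can be neither confirmed nor refuted.

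**5. Direction.** Let T be the actual PM+ t0–t1 interval, and take g as equal in both arms. The PM+ minus control difference is T − [(8 to 8.5) − g] = T + g − (8 to 8.5). It is the same for measures first taken at screening, since (T + g) − (8 to 8.5) is the same expression.

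- T = 8–8.5, like ends of the windows compared: difference = g, so control is shorter.
- T = 5–5.5 and g = 1: control t0–t1 is 7–7.5, so control is longer by 2 weeks.
- T + g = 8–8.5: no difference. Here the Timescale rule would balance the arms and the Measures/outcomes equivalence would be the loose statement.

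The two sections give equal intervals together only at g = 0.

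**The case against.** The strongest reply is that the control rule may be a deliberate attempt to match the PM+ calendar. Two weeks to the first session, five session-weeks and 1–1.5 weeks add to 8–8.5 weeks from consent, or from screening if the two are close together. On that view the arms are aligned and only the parenthesis in Measures/outcomes is imprecise. The text does not say so, but it does not exclude it. This stands as a reason not to claim a known direction. It does not remove the contradiction, because one of the two statements must still change.

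A reader might infer that control follow-up is systematically shorter and that the comparison is therefore biased toward PM+. That needs the Measures/outcomes interval to be true for PM+, which cannot be checked without the session spacing. A reader might also infer that 8–8.5 weeks is arithmetically wrong, but that again rests on an assumed spacing. Nor can the imbalance be put into PHQ-9 points, since the protocol gives no rate of change without treatment.

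The consequences are also limited. The trial is about feasibility and clinical outcomes are secondary. No power calculation is made and inference testing is limited. There is one VDC per arm, so arm and cluster are confounded whatever the timing. The full trial is to be powered mainly on effects of public health relevance, and data are not carried forward. All of this stands and keeps the severity down.

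**Conclusion.** The protocol contradicts itself on when t1 occurs, and following Timescale as written does not ensure the same t0–t1 interval in both arms. That conclusion rests only on the wording, the order of steps and Tables 4 and 5.

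The size is conditional. If PM+ t1 is truly 8–8.5 weeks after t0, control t0–t1 is shorter by g, and PM+ screening–t1 for GHQ-12 and WHODAS is longer by g. The 1- and 2-week values of g are illustrations, and larger gaps are possible because the lag from screening to trial consent is not stated. If PM+ t1 falls earlier, the imbalance can vanish or reverse. Sign and size are therefore not established.

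Severity is moderate. The descriptive between-arm change estimates and the timing procedure that may be carried into the full trial are affected; the feasibility progression criteria are not.

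**What to change.** 1. Reconcile Measures/outcomes and Timescale on one origin. Schedule control t1 from t0, at the t0–t1 interval that the PM+ session calendar actually gives, and keep the window of 1–1.5 weeks after session five for PM+. This replaces the rule that counts from screening.
2. Check the 8–8.5 weeks against the session calendar and correct it if it does not agree. Simply imposing 8–8.5 weeks from t0 on everyone is not safe: if the calendar gives a shorter interval, PM+ participants would miss the window after session five, which the Abstract also states as 7–10 days.
3. Record actual dates, and report by arm the t0–t1 interval and, for GHQ-12 and WHODAS, the screening–t1 interval. A common t0 origin equalises the latter only if the screening-to-baseline gap is similar in the two arms.

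The cost is schedule wording and visit-date logic on the tablets, with some control visits moving. Recruitment was already open when the article was written, so recording actual dates also makes follow-ups booked under either rule interpretable.
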